## Abstract

**Background:**

Postoperative delirium (POD) is the most common neurological adverse event among elderly patients undergoing surgery. POD is associated with an increased risk for postoperative complications, long-term cognitive decline, an increase in morbidity and mortality as well as extended hospital stays. Delirium prevention and treatment options are currently limited. This study will evaluate the effect of transcranial electrical stimulation (tES) on the incidence of POD.

**Methods:**

We will perform a randomized, double-blind, sham-controlled trial using single-session postoperative application of tES in the recovery room in 225 patients (> 65 years) undergoing elective major surgery. Patients will be randomly allocated (ratio 1:1:1) to one of three study groups: (1) alpha-tACS over posterior parietal cortex [2 mA, 20 min], (2) anodal tDCS over left dorsolateral prefrontal cortex [2 mA, 20 min], (3) sham [2 mA, 30 s]. Delirium will be screened twice daily with the 3-min diagnostic interview Confusion Assessment Method (3D-CAM) in the 5 days following surgery. The primary outcome is the incidence of POD defined as at least one positive screening during the five first postoperative days compared between tACS and sham groups. Secondary outcomes include delirium severity, duration, phenotype, postoperative pain, postoperative nausea and vomiting, electroencephalographic (EEG) markers, and fluid biomarkers.

**Discussion:**

If effective, tES is a novel, easily applicable, non-invasive method to prevent the occurrence of POD. The comprehensive neurophysiological and biofluid assessments for markers of (neuro-)inflammation and neurodegeneration will shed light on the pathomechanisms behind POD and further elucidate the (after-)effects of tES. The potential implications for the postoperative recovery comprise enhanced patient safety, neurocognitive outcome, perioperative manageability but also reduced healthcare costs.

**Trial registration:**

German Clinical Trial Registry DRKS00033703. Registered on February 23, 2024.

## Introduction

### Background and rationale {6a}

Current demographic scenarios assume that the population over the age of 65 will multiply by three by 2050 and their share of the population will reach 20% [1]. Patients in this age group are at particularly high risk of developing postoperative delirium (POD) after elective surgery [2]. Clinically, POD manifests as a disturbance of consciousness and attention with an acute onset and fluctuating course. In addition, POD is a risk factor for treatment-associated complications, for long-term cognitive deficits, and for the development of care dependency [3–5]. Despite these risks, the amount of major surgery in elderly patients is increasing [6]. This can be seen impressively in the increase in spinal operations, some of which are being performed up to 28 times more frequently on elderly patients compared to the 1990s [7].

Research findings point to a multifactorial model of delirium pathogenesis that encompasses neural aging, neuroinflammation, and endocrine stress responses, resulting in two critical aspects: neuronal neurotransmitter disbalances and network dysfunctions [8, 9]. These changes are reflected in biofluid and neurophysiological biomarkers [10, 11]. In particular, perioperative electroencephalogram (EEG) recordings suggest that disconnectivities in the alpha frequency band (8–12 Hz) may play a role in the pathophysiology of POD [12].

The pharmacological treatment of delirium is currently limited to symptomatic measures. The evidence on the benefit of medication is limited and the use of antipsychotics is not a causal treatment of delirium, but only serves to control symptoms [13]. Drug therapy with centrally acting drugs is therefore primarily used to dampen overly agitated behavior and to allow the implementation of necessary therapeutic measures [14]. Therefore, various strategies have been developed to prevent POD. Importantly, monitoring intraoperative cerebral activity with a frontal EEG allows individualized adjustment of anesthetic and analgesic administration to avoid overdosing [15]. Optimization of further perioperative factors such as polypharmacy, noise exposure, pain, and early postoperative reorientation support can also reduce the incidence of POD [16].

Non-invasive transcranial electrical stimulation (tES), in particular the application of a weak direct (transcranial direct current stimulation, tDCS) or alternating current (transcranial alternating current stimulation, tACS) via surface electrodes attached to the scalp, has shown promising results in the treatment of neurological diseases, including amelioration of age-associated cognitive deficits and chronic pain [17–21]. Through the interaction of weak currents with ongoing neural processes, tES has the potential to modulate brain plasticity, neuronal network architecture, and cerebral blood flow, thus exerting effects on neural processes that underly pain perception and higher-order cognitive functions [22–24].

During tACS, the oscillating current within a certain physiological frequency range interacts with ongoing cortical activity [25, 26]. tACS appears to modulate the amplitude, phase, coherence, and synchrony of ongoing oscillations and can hereby influence entrainment mechanisms [25–28]. This can support interregional synchronization, long-range neuronal coupling and thereby promote successful information transmission, improving cognitive function [29–31]. Anodal tDCS over task-relevant brain regions can influence cell membrane potentials and increase cortex excitability by inducing long-term potentiation (LTP)-like processes that outlast the stimulation interval [32]. Animal models suggest altered tissue density due to altered neuronal morphology, altered glial cell activity, and reorganization of synaptic connections in terms of neuroplastic phenomena induced by tDCS [33, 34]. In the only trial to date using tES in patients at risk to develop POD, Tao and colleagues observed a strong effect of postoperative single-session anodal tDCS over the left dorsolateral prefrontal cortex (DLPFC) on the incidence of POD and postoperative pain [35].

## Objectives {7}

The objective of this study is to investigate the effects of tES on the incidence of POD and postoperative pain. As primary objective, the effect of tACS in the alpha frequency range (alpha-tACS) on the incidence of POD after major surgery will be examined in comparison to sham stimulation. In a second study arm, the effect of tDCS compared to sham stimulation on the incidence of POD will be investigated. The effect of tES on postoperative pain will be investigated as a secondary outcome, for both intervention groups in comparison to sham stimulation. To identify potential predictors of the responsiveness to tES and to address the multifactorial genesis of POD and postoperative pain, we plan to assess neuronal network dysfunction with pre-, intra-, and postoperative EEG recordings but also neurotransmitter disbalance and neuroinflammation/-destruction using biofluid blood biomarkers. Furthermore, the influence of intraoperative medication, type and length of surgery, and vital parameters on the endpoints will be considered. Potential predictors of response to tES will thus be identified.

## Trial design {8}

This study is a prospective, monocentric, randomized, double-blind, sham-controlled clinical trial within a “superiority” framework. The trial aims to assess whether transcranial electrical stimulation (tES) can reduce the incidence of postoperative delirium (POD) and postoperative pain compared to sham stimulation.

Data collection will occur preoperatively, intraoperatively, and over the first 5 postoperative days. Three trial arms with different types of stimulation intervention will be included: alpha-tACS, tDCS, and sham stimulation with an allocation ratio of 1:1:1.

Patients will undergo a single postoperative tES stimulation (with 2 mA) for 20 min in the post-anesthesia care unit (PACU). We will undertake perioperative EEG recordings and blood sampling at three different timepoints. POD and postoperative pain will be screened for 1 h in the PACU as well as twice daily for 5 days after surgery.

## Methods: participants, interventions and outcomes

### Study setting {9}

Single center study of the Greifswald University Hospital (UMG), Germany. The study has been approved by the local ethics committee with the registration number BB 179/23 on December 8, 2023.

Greifswald University Hospital is a tertiary care center that treats a high volume of patients. It has established a dedicated Delirium Prevention Unit as part of routine care, with a special focus on elderly and at-risk patients undergoing surgery. This unit integrates prevention strategies across multiple departments, providing extensive clinical and research expertise in managing delirium. These characteristics make the hospital an ideal setting for investigating the effects of transcranial electrical stimulation on postoperative delirium.

### Eligibility criteria {10}

#### Inclusion criteria

Patients over 65 years of agePlanned elective general surgery, urological, gynecological, orthopedic, or spinal procedures lasting more than 60 min (major surgery)Capable of providing consentPresence of a signed informed consent form

#### Exclusion criteria

Known neurological or psychiatric conditions, especially history of epileptic seizuresContraindications for tDCS/tACS application [27]Long-term medication with central nervous system (CNS) active drugsIsolation due to multidrug-resistant germsInability of the patient to read and/or speak German

### Who will take informed consent? {26a}

Screening will take place at the anesthesia outpatient clinic and the inpatient wards of the Greifswald University Hospital during preoperative anesthesia consultations.

After checking the inclusion and exclusion criteria, handing out, and orally explaining the patient information, consent to participate in the study will be requested. Patients will be enrolled after signature of the informed consent form. Subsequently, an identification number will be assigned for pseudonymization.

### Additional consent provisions for collection and use of participant data and biological specimens {26b}

The informed consent form comprises specific sections about the use of biological specimens and patient data. It explains the handling of the biological specimens, stating that the blood samples will be processed using the assigned pseudonyms and stored during the conduction of the trial in the biobank of the Greifswald University Hospital. Subsequently, the intended parameters will be determined, and the blood samples destroyed to ensure data minimization. Informed consent form details the handling of patient data and accords with the General Data Protection Regulation (GDPR).

## Interventions

### Explanation for the choice of comparators {6b}

The choice of comparators in this study, involving alpha-tACS, tDCS, and sham stimulation, is grounded in the need to comprehensively evaluate the efficacy of tES protocols in preventing POD. Alpha-tACS and tDCS were selected based on their demonstrated potential in modulating brain activity, which is crucial to address the pathophysiological mechanisms underlying POD.

The alpha-tACS intervention was chosen based on the previously described disrupted neural network connectivity in the alpha range associated with POD [36].

tDCS applies a constant electrical current, which can modulate neuronal excitability and has been shown to reduce postoperative pain and the POD incidence when applied postoperatively [35].

The sham stimulation serves as the control condition. The sham procedure mimics the application of the active interventions without delivering the electrical current, ensuring that participants, care providers, and outcome assessors are blinded to the intervention.

### Intervention description {11a}

Patients will be enrolled at least 1 day before surgery. Questionnaires regarding contraindications for tES as well as baseline questionnaires will be handed out (PPI, HADS, STAI, PCS, BRI, PSQ, DN4). The preoperative cognitive status will be assessed with a MoCA score.

On the day of the surgery, a 64-channel EEG will be recorded in the preoperative holding area. Preoperative delirium and pain will be assessed with standardized tests (RASS, 3D-CAM, and NRS). A preoperative blood sample will be drawn. Before induction of anesthesia, a frontal EEG recording will be started that will last until the end of anesthesia.

A single tES intervention will take place postoperatively in the PACU, after return of consciousness and patient handover to the PACU staff. Emergence of delirium in the PACU (PACU-D) will be assessed, and patients will be asked about postoperative nausea and vomiting (PONV) as well as pain using standardized tests (RASS, 3D-CAM, and NRS) every 30 min for 1 h in the post-anesthesia care unit (PACU). A 64-channel EEG will be recorded, and a second blood sample will be drawn after the tES intervention.

During the first 5 postoperative days, patients will be screened twice daily for POD and pain using standardized tests (RASS, 3D-CAM, and NRS). A third blood sample will be drawn on the second postoperative day (Fig. 1).

**Fig. 1 Fig1:**
[figure not shown]
Timeline of the study interventions and visits. PACU post-anesthesia care unit, EEG electroencephalography, tES transcranial electrical stimulation, RASS Richmond Agitation-Sedation Scale, 3D-CAM 3-min diagnostic interview Confusion Assessment Method, NRS Numerical Rating Scale

#### Baseline questionnaires

A questionnaire regarding contraindications for the application of tES will be filled out by the physician enrolling the patient. It comprises questions regarding presence of metallic implants, history of neurosurgical intervention, traumatic brain injury or epileptic seizures, known dermatological disorders, ongoing long-term medication, possibility of a pregnancy, and previous tES application.

A set of questionnaires regarding pain (NRS, DN4), attitude towards pain (PCS, PSQ), and affective disorders (HASD, STAI) will be explained and handed out to the patient.

The Montreal Cognitive Assessment (MoCA) score evaluates cognitive functioning in areas such as attention, memory, language, and visuospatial skills. It will be conducted and scored by a trained study personnel.

#### EEG

A 5-min resting-state EEG with eyes closed will be recorded preoperatively in the holding area and post-intervention in the PACU. EEG data will be recorded using ANT Neuro’s dry EEG system, equipped with dry surface electrodes that do not require the use of conductive gel or paste. This system is designed for a rapid setup, allowing for signal acquisition in this clinical setup. Patients will be lying in bed, and the dry EEG cap, fitted with 64 electrodes according to the 10–20 international system, will be placed on their head. The electrode positions will be adjusted to ensure optimal scalp contact. Patients will be asked to remain still and relaxed, with eyes closed during the recording session of 5 min. Data acquisition will be conducted at a sampling rate of 1064 Hz. The impendences will be monitored and maintained below an ideal threshold of 5 kΩ if possible or the recommended threshold of 100 kΩ.

Intraoperatively, a frontal EEG will be recorded with a common neuromonitoring tool available at the study site (SedLine® Brain Function Monitor by Masimo or Narcotrend®-Compact M by Narcotrend-Gruppe). Both medical devices are used to monitor the brain function of patients under anesthesia or sedation in critical care settings, utilizing raw and quantitative EEG parameters to provide a real-time dimensionless index of sedation depth. Before the start of the recording the study staff ensures the proper functioning of the monitor. For the SedLine Monitor, we will make sure that the feed speed is set at 30 mm/s and the amplitude at 5 mV, since the display settings affect the sampling frequency of the recorded data stored [37].

#### Intervention

The tES will be administered using a battery-powered stimulator (Neuroelectrics® Starstim Home Research Kit, Barcelona, Spain) via two electrodes (5 cm in diameter) soaked with 0.9% NaCl solution and mounted in a neoprene cap.

To ensure blinding to the stimulation group, the ECG monitoring in the PACU will be masked before the start of the intervention with a stencil covering the raw ECG traces.

In the tACS group, two electrodes will be placed at the P3 and P4 positions of the 10–20 EEG system, over the respective left and right posterior parietal cortex (PPC) (Fig. 2B). A 20-min oscillating stimulation with 2 mA (peak-to-peak) at an age-adapted frequency of 9.5 Hz will be applied. An age-adapted stimulation frequency was determined for this cohort by analyzing a database of 532 clinical resting-state physiological EEG recordings. The method was described in detail elsewhere [38]. In the tDCS group, the anode will be placed over the left DLPFC, as determined by the F3 position of the 10–20 EEG system. The cathode will be placed over the right supraorbital area, corresponding to Fp2 of the 10–20 system (Fig. 2A). The 20-min continuous stimulation with 2 mA will gradually increase and decrease at the beginning and end within an additional 10-s period (ramp time).

**Fig. 2 Fig2:**
[figure not shown]
Illustration of electrode placement and electric field distribution. Applied transcranial electrical stimulation on an MNI head/brain for (**A**) tACS group (stimulation frequency: 9.5 Hz; electrodes centered over P3 and P4; electrode diameter: 5 cm) and (**B**) tDCS group (electrodes centered over F3, anode, and Fp2, cathode; electrode diameter: 5 cm), simulated using SimNibs [58, 59]. tACS transcranial alternating current stimulation, tDCS transcranial direct current stimulation

The sham group is divided into two subgroups with n(tDCS)/2 for tDCS-sham and n(tACS)/2 for tACS-sham. In these subgroups, the same electrode arrangements and ramp times are used, but the current is only applied for 30 s to induce the typical tingling sensation on the scalp and blind the patients to the stimulation condition.

The perception of side effects associated with the stimulation and group affiliation is surveyed at the end of each stimulation condition using a standardized questionnaire [27].

#### Blood samples

Three blood samples will be taken for the study: one preoperatively, one postoperatively in the PACU, and one on the second postoperative day, with 5 mL of serum collected each time. The blood samples will be sent immediately after collection to the Greifswald University Hospital biobank for aliquoting and storing. The following parameters will then be determined from these samples in the neurology research laboratory of the Greifswald University Hospital: VILIP-1, CCL2 (MCP-1), sTREM-2, BDNF, TGF-β1, VEGF, IL-6, sTREM-1, β-NGF, IL-18, TNF-α, sRAGE, CX3CL1, CRP, NfL, S100b, VCAM-1, ECAM-1. The samples will be destroyed after measurement.

#### Postoperative visits

The RASS, the 3D-CAM, and the NRS score will be assessed once preoperatively in the holding area, every 30 min for 1 h in the PACU (3 times in total) as well as twice a day for 5 days postoperatively.

The Richmond Agitation-Sedation Scale (RASS) score is a commonly used tool to assess a patient’s level of agitation or sedation, ranging from + 4 (combative) to − 5 (unarousable), with 0 representing an alert and calm state [39]. Patients with a postoperative RASS score in the PACU of − 2 or below will not be questioned regarding POD or pain.

The 3D-CAM is a reliable, validated diagnostic assessment tool for delirium, based on a structured 3-min interview to identify the presence of POD and was translated and validated for the use in German [40, 41]. Based on the principle of the CAM method, “(…) the algorithm is considered positive if following features are present: Feature 1) Acute onset or fluctuating course and Feature 2) Inattention and either Feature 3) Disorganized thinking or Feature 4) Altered level of consciousness.”

If a patient is identified as delirious based on the 3D-CAM, the RASS score will be used to determine the phenotype of the delirium at the timepoint of the visit: hypoactive (RASS − 5 to − 1) or hyperactive (RASS + 1 to + 4).

Furthermore, the 3D-CAM-S score will be calculated from the 3D-CAM assessment. The 3D-CAM-S is a validated method derived from the 3D-CAM diagnostic interview for assessing delirium severity, demonstrating excellent agreement with the commonly used delirium severity scale, CAM-S Short Form, and is designed to provide prognostic information, monitor delirium progression, and evaluate treatment response in older patients undergoing major elective non-cardiac surgery [42].

The Numeric Rating Scale (NRS) is a self-report measure of pain intensity on a scale of 0 (no pain) to 10 (worst possible pain), used for assessing a patient’s self-reported pain level.

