#### Secondary outcome measures

Duration of POD (days between first positive 3D-CAM score and last positive 3D-CAM score)Maximal POD severity (3D-CAM-S)Median and interquartile range of POD severity (3D-CAM-S)Delirium phenotype (RASS)Adverse eventsIncidence of emergency delirium in the PACU (PACU-D) as defined by having at least one positive 3D-CAM score in the PACUPostoperative pain in the PACU (NRS)Postoperative pain in the five first postoperative days (NRS)Presence of postoperative nausea and vomiting (PONV)EEG biomarkers from postoperative 64-channel EEG recordings including but not limited to total power, power within frequency bands, measures of periodic activity (power, center frequency, bandwidth), measures of aperiodic activity (offset, exponent), phase-lag-index, entropy measures, and burst-suppression-ratioPostoperative blood biomarkers

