#### Secondary outcome analysis

Binary logistic regression will be employed to adjust for baseline delirium status and to test differences between treatment (tDCS) and control (sham) in incidence of POD. Dependent variable will be incidence of POD (yes/no); independent variables are group (tDCS/sham) and baseline delirium status as measured by the 3D-CAM score. Odds ratio and corresponding 95% CI will be reported.Continuous variables (e.g., duration of delirium, severity scores, EEG biomarkers, fluid biomarkers) will be analyzed using analysis of covariance (ANCOVA) including the particular baseline value.Categorical variables (e.g., delirium phenotype) will be analyzed using binary logistic regression, adjusting for baseline 3D-CAM.For EEG and biofluid biomarker outcomes, linear mixed-models (LMM) will be implemented to account for within-subject correlations across time points.

In addition to the primary and secondary outcomes, exploratory analyses will be conducted on the collected blood samples to gain further insights into the biological mechanisms associated with postoperative delirium (POD) and the effects of transcranial electrical stimulation (tES). These analyses will focus on identifying associations between levels of various blood biomarkers—particularly markers of neuroinflammation, neurodegeneration, and other relevant pathways—and the incidence and severity of POD. Additionally, we aim to explore potential biomarkers that may be associated with differential responses to the tES intervention.

To better understand how patient characteristics influence treatment response, we will conduct subgroup analyses using blood biomarker profiles. These profiles, identified through exploratory cluster analysis, will help us group patients into distinct subgroups with potentially unique responses to tES. This approach could uncover specific biomarker patterns linked to differential treatment effects, paving the way for personalized POD prevention strategies. Recognizing the heterogeneity of our study population is crucial for interpreting our findings and guiding future research towards biomarker-driven, individualized treatments [45]. Our discussion will highlight the importance of considering patient diversity in POD risk and treatment response.

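### Delirium phenotype has no class for a delirious patient at RASS 0, and a hypoactive-versus-hyperactive regression would compare only patients who became delirious

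*Protocol article*

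**What the plan says.** All places are in the protocol article.

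- **Postoperative visits (under Intervention description {11a}).** Phenotype is derived only after a positive 3D-CAM, in which case "the RASS score will be used to determine the phenotype of the delirium at the timepoint of the visit". The two classes are "hypoactive (RASS − 5 to − 1) or hyperactive (RASS + 1 to + 4". The same section describes the RASS as running from +4 to −5, "with 0 representing an alert and calm state". The delirium algorithm it quotes needs acute onset or fluctuating course, plus "Inattention and either Feature 3) Disorganized thinking or Feature 4) Altered level of consciousness".
- **Secondary outcome measures {12}.** The list includes "Delirium phenotype (RASS"), with no further definition.
- **Secondary outcome analysis {20a}.** "Categorical variables (e.g., delirium phenotype) will be analyzed using binary logistic regression, adjusting for baseline 3D-CAM".
- **Statistical methods {20a}, opening paragraph.** The analysis follows intention to treat and includes every randomised patient in the assigned group.
- **Sample size {14}.** The planning rates are 19.7% and 4.9%, with 60 patients per group and 225 in total after about 20% dropout. The local POD prevalence is given as 22.2%.

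**The concern.** There are two separate problems.

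First, the class definition does not cover its own scale. It is written out in full, with numerical limits on both sides, and omits 0. The omission matters only if a patient can be delirious at RASS 0, and the quoted algorithm allows that. A two-class outcome has no place for such a patient. The choice between dropping and assigning would then be made during analysis, where it can move the result of a comparison with very few cases.

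Second, phenotype is undefined in a patient who never screens positive. The direct reading of a binary model for phenotype is hypoactive versus hyperactive among delirious patients. Stimulation is expected to change who becomes delirious, so the delirious patients in the two arms would no longer be comparable through randomisation. A difference in phenotype mix could then arise only from which cases were prevented.

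**Working it through.** **Step 1. Does the definition cover the scale?** RASS takes the values −5 to +4. The hypoactive class takes −5 to −1 and the hyperactive class takes +1 to +4. The value left over is 0, the alert and calm state.

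**Step 2. Can a delirious patient be at RASS 0?** The quoted rule is positive if Feature 1 and Feature 2 are present together with Feature 3 or Feature 4. Features 1 + 2 + 3 (acute or fluctuating course, inattention, disorganised thinking) therefore suffice without Feature 4 (altered level of consciousness). Nothing in the article excludes RASS 0 for such a patient or assigns a class.

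**Step 3. Reproduce the plan's own figure.** Inputs: p1 = 0.197, p2 = 0.049, one-sided α = 0.05, power 80%. The mean rate is 0.123.

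n = [1.645·√(2·0.123·0.877) + 0.842·√(0.197·0.803 + 0.049·0.951)]² / (0.197 − 0.049)²

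This gives about 59.8, so 60 per group, as stated. Dropout: 60/0.80 = 75 per arm, and 3 × 75 = 225, as stated.

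**Step 4. How many patients have any phenotype?** Expected delirious patients = n × rate.

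| Patients per arm | Sham, 19.7% | Sham, 22.2% | tACS, 4.9% |
|---|---|---|---|
| 60 | 11.8 | 13.3 | 2.9 |
| 75 | 14.8 | 16.7 | 3.7 |

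At 60 per arm that is about 12 against 3. The active arm keeps 4.9/19.7 = 25% of the sham arm's cases. The chance that 60 tACS patients include at most one delirious patient is 0.951^60 + 60·0.049·0.951^59 ≈ 0.049 + 0.152 = 0.20. In about one trial in five, the tACS side would hold one case or none.

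**Step 5. What does conditioning on delirium do?** As an illustration only, assume that the 12 sham cases split 6 hypoactive and 6 hyperactive. The article gives no split. Let h of the 3 tACS cases be hypoactive, with h from 0 to 3.

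- Among delirious patients, the hypoactive share is 6/12 = 50% in sham and h/3 in tACS, so anywhere from 0% to 100%.
- Among all randomised patients, the hypoactive risk is 6/60 = 10% in sham and h/60 in tACS, so at most 3/60 = 5%.

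At h = 3 the first comparison suggests that stimulation shifts patients towards hypoactive delirium (100% against 50%), although the risk of hypoactive delirium has halved. Only the second comparison keeps the randomised groups.

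**The case against.** The strongest reply is that the article does not say the regression is restricted to delirious patients. The analysis section names no analysis set or unit for phenotype, and the general statement covers all randomised patients. A model for hyperactive POD yes or no in everyone would fit both. This stands, and it makes the selection point conditional. It does not touch the RASS 0 gap, which no other section closes.

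A second reply is that a rule for combining visits into one phenotype per patient is usual SAP content, and the SAP is not shown. This also stands. The absence of that rule is not counted here. A reader might infer that patients with both types at different visits are discarded, but no such rule is written.

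A reader might also be drawn to two stronger readings.

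- **PACU.** Patients in the PACU at RASS −2 "or below will not be questioned regarding POD or pain", so it may seem that hypoactive cases are hidden. That restriction applies only in the PACU. POD is defined over the 10 visits in the 5 postoperative days, PACU delirium is a separate secondary outcome, and nothing says that an unscreened check counts as negative.
- **Size of the RASS 0 loss.** It is tempting to apply an assumed share of RASS 0 cases to the roughly 15 delirious patients. The article gives no share. RASS 0 is also a state at a visit, and a patient has no class at all only if RASS is 0 at every positive visit. No count is supported.

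Finally, with so few cases any phenotype comparison will be close to descriptive. That is true, and it limits the weight of the point, but it does not justify an undefined outcome.

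**Conclusion.** The RASS 0 gap is certain from the text. The classes omit a value that the quoted delirium algorithm allows, and the binary model has no place for it. How many patients it affects is unknown.

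The selection point holds if the regression is run as hypoactive versus hyperactive. It would then rest on about 12 sham and 3 tACS patients, assuming 60 per arm and the planning rates (about 15 and 4 at 75 per arm). It would condition on a post-randomisation event and depart from the stated intention-to-treat principle.

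Phenotype is one of many secondary outcomes. The primary outcome, its analysis and the sample size are unaffected. The change is worth making because it is cheap and can be settled before unblinding.

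**What to change.** In the outcome definition, add a class for a positive 3D-CAM with RASS 0. In the analysis section, replace the single phenotype variable with three yes/no outcomes, each in all randomised patients:

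1. any hypoactive POD (at least one positive visit with RASS −5 to −1);
2. any hyperactive POD (at least one positive visit with RASS +1 to +4);
3. POD with RASS 0 at every positive visit, reported descriptively if sparse.

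A patient may count in both of the first two. Every patient with POD and a recorded RASS at the positive visits then falls into at least one outcome, and patients without POD are non-events in all three. Each outcome can use the logistic model already planned, with the same adjustment.

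The cost is wording in the outcome definition and the SAP. RASS and 3D-CAM are already scheduled together at every postoperative visit, so no new data collection is needed. The downside is a few more secondary analyses with few events, whose intervals will be wide.
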